#### Study group

Interested patients of the Child and Adolescent Psychiatry Department (BUGL) at The National University Hospital in Reykjavik the guardians and child will receive invitation letters with information about the MMM-study. In a follow-up phone call questions about the study can be answered and more information given. If interested to participate, an informed consent is signed, including a letter to the child’s teacher allowing the researcher to contact the teacher. For the healthy control groups (group I and II), a randomly selected child (matched by gender and age and within the same zip-code) will be contacted by the Social Sciences Research Institute (SSRI) and invited to participate similarly (control group I). Parents will be asked if a potential full sibling (+/-3 years) living in the same household could be included in the study (control group II) as we hypothesize that there are differences in other potentially relevant background factors comparisons with full siblings, and therefore, this will give insight into family variability. However, this is *not* a prerequisite for participation.

A kit including tools for collecting biosamples with good instructions and a booklet for the three-day dietary recording will be provided. In addition, links will be sent for demonstrating the specimen collection, however medical auxiliary will be available for assistance by request. Participants will be asked to be present for a blood test at the Landspitali-University Hospital in Reykjavik or Akureyri-Hospital, in Iceland, based on their residency. Eligibility criteria for the study and control groups are outlined in Table 1.

**Table 1 pone.0273855.t001:** Eligibility criteria for the MMM study.

Participant type	Inclusion criteria	Exclusion criteria
Cases	Children and adolescents 5–15 years, males, and females, referred for their first visit to the outpatient clinic at the Child and Adolescent Psychiatry Department (BUGL). Living in Reykjavik or Akureyri or surroundings.	Not speaking/understanding Icelandic language Recent use of antibiotics (within last 4 weeks)
Control group I: *Healthy controls*	Children and adolescents 5–15 years not diagnosed with mental disorders. Living in Reykjavik or Akureyri or surroundings.	Mental disorder diagnosis Recent use of antibiotics (within last 4 weeks)

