Control group II: *Parental siblings (full siblings*, *i*.*e*., *brothers and sisters)*	Full siblings living in the same household close in age to the study subjects (+3y) not diagnosed with mental disorders. Living in Reykjavik or Akureyri or surroundings.	Mental disorder diagnosis Recent use of antibiotics (within last 4 weeks)

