### Sample collection

All biosamples, except blood, will be collected at home by the participants, with help from their guardians when needed. A biosample kit will be delivered to the participants and collected by research staff to make sure the samples will be in good condition and usable. Participants are asked to collect the biosamples preferably towards the end of the 3-day food registration within the first month into the study and store the biosamples in a specific container in a cool dry place (4–8°C) according to the manufacture’s guidelines. Commercial kits from DNA Genotek´s microbiome stool collection kits are used to collect and optimally stabilize stool samples. Fecal and saliva samples will be collected for microbiome 16s rRNA amplicon sequencing. A buccal swab will be collected for whole-genome genotyping of human DNA. Urine samples will be collected for targeted analysis of food-related peptides and untargeted metabolomics profiling. Blood will be collected either at Landspitali, University Hospital in Reykjavik, or Akureyri Hospital in Akureyri, depending on residence, for analyzing serum zonulin, inflammatory biomarkers, e.g., CRP, interleukins, and nutritional status, i.e., hemoglobin, ferritin, folic acid, Vitamin B_12_, 25-hydroxy-vitamin-D, and fatty acids. The biosamples are preferable to be collected towards the end of the 3-day food registration according to standard procedure as mentioned above. The kit is then collected from both cases and controls by the researchers along with the food diary in Reykjavik, Akureyri, and near surroundings. Participants will be able to deliver the samples to a provided location if they prefer. For other locations in Iceland, the samples will be sent out, including guidelines on how to resend them to the researchers after their collection. The urine samples will be aliquoted into smaller tubes for storing at a laboratory unit at the University Hospital or Akureyri Hospital in a -80°C freezer along with the other biological samples.

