## Discussion

Investigating the interaction between diet, intestinal microbiota, IP, and their associations with mental health and comparison to healthy controls is an original and novel study. The Child and Adolescent Psychiatry Department (BUGL) at Landspitali, the National University Hospital of Iceland is the *only* psychiatric department for children and adolescents. This is the first population-based study enrolling all children with the most severe mental disorders assessed both categorically and dimensionally for one year and matched controls. This approach will provide valuable information on the relationship between these three domains offering crosstalk between different disciplines, to identify novel associations and potential mechanisms involved in neurodevelopmental disorders. There is a call for more population-based multidimensional transdisciplinary studies designed for improving mental health and our study fits well with priorities recently put forward in the Roadmap for Mental Health Research in Europe [166]. Furthermore, the World Health Organization (WHO) has recently called for a stronger focus on adolescent’s health, with depression as the number one cause of illness and disability in this age group [167]. Along with increasing the amount and precision of clinical information collected, the longitudinal approach of the MMM study will improve both reliability and validity of psychiatric diagnoses in line with LEAD (Longitudinal, Expert, All Data) procedure [168]. Furthermore, collection of multi-omics data and clinical correlates otherwise missing in this unique study population is of importance. Repeating data collection in the same groups in three years, when majority of children will be in their adolescence, gives a valuable opportunity to observe changes especially as studies on mental health are lacking in this age group [169, 170]. More multidimensional transdisciplinary studies including longitudinal observational data have been called for as a basis for lifestyle treatment options for improving mental health and wellness [169, 170]. Importantly, the longitudinal design also allows for determining if the baseline dietary, microbiome, and metabolome patterns are predictive of future outcomes, which may aid the definition of biomarker-based diagnostic tools and therapeutic interventions. The novelty of this longitudinal observational case-control study in children and adolescents resides in the new way of approaching mental disorders holistically. Using longitudinal experts diagnoses with simultaneous use of categorical and dimensional assessments using recognized and validated rating scales, identifying patterns between the leading players of meals, intestinal microbiota, IP, and mental health has never been done before. The strengths and limitations of this study are outlined in Table 3.

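### Table 1 excludes non-Icelandic speakers among cases only, so control group I may include children who could not have been cases; separately, its residence limit conflicts with other sections

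*Protocol article*

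**What the plan says.** **Language.** Table 1 (Methods, Study group) gives eligibility by participant type. For cases, the exclusions are "Not speaking/understanding Icelandic language" and antibiotic use in the last four weeks. For control groups I and II, the exclusion cell reads "Mental disorder diagnosis Recent use of antibiotics (within last 4 weeks" and contains no language criterion.

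**Who the controls are.** Control group I is "a randomly selected child (matched by gender and age and within the same zip-code", contacted by a research institute. Control group II is "Full siblings living in the same household close in age to the study subjects".

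**Residence.** Each of the three rows of Table 1 requires "Living in Reykjavik or Akureyri or surroundings". The Sample collection section has staff pick up the kit "along with the food diary in Reykjavik, Akureyri, and near surroundings", and then adds: "For other locations in Iceland, the samples will be sent out". The section on study population and recruitment invites every child of 5 to 15 years referred to the department over one year and states no residence limit. The Discussion says: "This is the first population-based study enrolling all children with the most severe mental disorders".

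**The concern.** Controls in a case-control study should come from the population that would have supplied the cases. An eligibility rule applied to cases alone breaks that link: a child in control group I who does not speak Icelandic could not have entered as a case. If such children tend to eat differently or carry a different microbiota, the comparison of cases with control group I picks up a difference that has nothing to do with mental disorder. Diet and microbiota are among the domains the study sets out to compare. The food frequency questionnaire is built for the Icelandic food environment, so it may also measure less well in these families.

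The residence conflict is a separate matter. It leaves unclear who is enrolled and to which children the results apply.

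**Working it through.** **1. The plan's own figure.** The only powered comparison is 30% against 10% with altered intestinal permeability, at α = 0.05, 80% power and a 1:1 ratio (Sample size section). The usual two-sided formula without continuity correction is

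n = [z₀.₉₇₅·√(2·0.20·0.80) + z₀.₈₀·√(0.30·0.70 + 0.10·0.90)]² / (0.30 − 0.10)²

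= [1.960·0.5657 + 0.8416·0.5477]² / 0.04 = 61.6, rounded up to 62 per arm.

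This reproduces the stated 62. The language point does not alter it. The target of at least 100 per arm is used below.

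**2. Table 1, row by row.**

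| Criterion | Cases | Control I | Control II |
|---|---|---|---|
| Recent antibiotics excluded | yes | yes | yes |
| Residence in the two areas | yes | yes | yes |
| No Icelandic: excluded | yes | not listed | not listed |

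The table repeats the antibiotic and residence criteria in every row. The absence of the language criterion from two rows is therefore what the document states, and is not explained by a shared criterion being listed once.

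**3. Does another provision close the gap for control group I?** Matching is on gender, age and zip code, not language. The confounders named in the integrative analysis section are age, sex, body mass index, ROME IV, medication and diet. The list is open-ended, but language and origin are not named. No stated rule closes the gap.

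**4. Control group II.** These are full siblings living with the case, so a different language and food background is largely ruled out.

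**5. Size, under assumptions.** Neither input is in the documents. Let f be the share of control group I that does not speak Icelandic, and d the amount by which these children differ from the rest, in SD of a diet or microbiota measure. The shift in the mean contrast is f × d. With 100 per arm the standard error of a standardised difference is √(2/100) = 0.141. The chance of a false positive at a nominal two-sided 5% level is Φ(−1.96 + f·d/0.141) + Φ(−1.96 − f·d/0.141).

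| f (assumed) | d (assumed) | Shift, SD | False-positive rate |
|---|---|---|---|
| 5% | 0.5 | 0.025 | 5.4% |
| 10% | 0.5 | 0.05 | 6.4% |
| 15% | 0.5 | 0.075 | 8.3% |
| 15% | 1.0 | 0.15 | 18.6% |

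At a 2% share and 0.5 SD the shift is 0.01 SD and the rate is 5.1%. These rates are for one unadjusted comparison, before the planned false discovery rate correction.

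**6. Residence, side by side.** Table 1 admits only residents of two areas. The Sample collection section describes staff pick-up in those areas and a mail route for elsewhere in the country. The recruitment section invites all referrals, and the Discussion describes the department as the only one of its kind. A family outside the two areas is thus invited under one section, provided for under another and ineligible under Table 1. The conflict reaches the controls too: a case from elsewhere would need a control from the same zip code, whom Table 1 bars.

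**The case against.** - **Practical screening.** Control group I is invited in a similar way to cases and completes the same instruments, described as validated in Iceland. Records lacking key diet data may be removed. This probably keeps the number of non-speakers low. That stands as a reason to expect a small effect, but no rule says that non-speakers are excluded.
- **Language is not origin.** A bilingual child of foreign background is eligible as a case, so the criterion does not make cases culturally uniform, and extending it would not equalise diet between groups. That stands. The fix restores equal eligibility and does not remove every cultural difference.
- **Adjustment is possible.** Background factors are collected and the confounder list is open. Adjustment is therefore not precluded, but neither is it planned for language.
- **Residence is a matter of wording.** Surroundings is undefined and may be wider than near surroundings. Even so, it does not comfortably cover other locations in the country. The Discussion's claim is partly tempered elsewhere: all are invited, diagnoses of all patients are recorded to detect selection, and willingness to participate is listed as a limitation.

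A reader might infer that a bias is built into every case-control contrast, or that it is a large part of the effect the study can detect. The documents support neither. The sibling contrast is largely protected. For control group I the bias is possible, not certain, and a large value appears only when both assumed inputs are set high.

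**Conclusion.** The asymmetry in Table 1 is real and can be read directly from the text. It matters for the comparison of cases with control group I, where it permits a non-disease difference in diet or microbiota. Its size is unknown. Under assumed shares of 5-15% and assumed differences of 0.5-1 SD it would be about 0.03-0.15 SD, and it is negligible if few controls are non-speakers. The stated sample size is unaffected. The residence conflict is also real: Table 1, the recruitment section and the Sample collection section cannot all hold as written. No effect on a particular result has been shown for it; what it affects is who is enrolled and how far the results generalise. Both points should be corrected, and neither invalidates the design.

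**What to change.** **Language.** Add the case criterion to the exclusion cell for control group I, and write it for control group II for consistency. Ask one screening question at control recruitment. For controls already enrolled, record language and run the case versus control I comparison restricted to children who meet the case criterion.

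**Residence.** Reconcile Table 1 with the recruitment and Sample collection sections so that one rule holds for cases and for their zip-code-matched controls. Then make the Discussion's description of the sample match that rule. If the two-area limit stays, the mail route goes and the claims to all children and to a population base are qualified. If the limit is dropped, Table 1 changes in all three rows.

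**Cost.** Two table cells, one screening question, a restricted analysis if non-speakers are already enrolled, and a few sentences on residence. A few controls may have to be replaced.

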#### Sample size

Power calculations were performed for detecting mean difference (independent sample t-test) intestinal permeability using unmatched case-control with an ⍺ of 0.05 and β of 20% (i.e., power of 80%) with 1:1 ratio of cases vs. controls [123, 124]. The prevalence of IP among cases was calculated at 30%. However, assuming 10% prevalence in controls, the minimum number of children in each arm of the study is 62. However, as our case group covers a relatively broad spectrum of mental disorders (often overlapping individually) that will be examined in smaller case groups, the aim is set at a minimum of 100 participants in each arm (70% participation rate). The current study is an observational and non-intervention study, and therefore it is not possible to calculate power for all the factors that will be compared between the cases and controls. Corrections will be made for multiple comparisons.

### Data collection

The project has been registered by the Icelandic National Bioethics Committee (VSN19-225) in Iceland and clinicaltrials.gov (NCT04330703). The MMM-study adheres to the “Strengthening the Reporting of Observational Studies in Epidemiology” (STROBE) guidelines. All participants, i.e., cases and controls, will complete a three-day food diary, validated questionnaire on frequency of food and supplement intake according to the ICEFFQII, which is designed for the Icelandic food environment [125, 126] as well as a validated questionnaire on physical ailments or diagnoses, based on a version of the ROME IV [127–129]. Questionnaires on atopic diseases, according to the iFAAM [130–132] and medication and other essential background factors, will be completed. The mental health questionnaires used in the study have all been validated internationally as well as in Iceland. These are teacher and parent reports and self-reports for children >10 years and are listed with other questionnaires in Table 2.

**Table 2 pone.0273855.t002:** List of patient-answered validated mental health questionnaires and other validated and non-validated questionnaires.

	The ADHD Rating Scales [133–135]
Validated teacher and parent-reports	The Child Behavior Checklist (TRF and CBCL) [136–139]
	The High-Functioning Autism Spectrum Screening Questionnaire (ASSQ) [140]
	The Social Responsiveness Scale (SRS) [141–144]
	The Children’s Depression Inventory (CDI) [145–149]
Validated self-reports for children >10y	The multidimensional Anxiety Scale for Children (MASC) [76, 150–155]
Other validated questionnaires	Food Frequency Questionnaires (ICFFQII) [125]
	ROME IV (shorter version) [127–129]
	Questionnaires on atopic diseases iFAAM [130–132]
Other non-validated questionnaires	Questionnaires on medication and other essential background factors

Furthermore, if allowed by the guardians, information on prescription medication dispensed for the child from birth to the current date will be retrieved from the Icelandic Medicine Registry (IMR). During the recruitment period, the diagnosis of all patients coming to BUGL will be recorded to detect potential selection biases in data collection. If the recruitment is delayed, the advisory board will meet to discuss possible actions. Quality checks will be performed throughout the period, as well as simple descriptive statistical analysis. Longitudinal data collection will take place three years after the first data collection. The participants will be contacted again to collect data from both cases and controls.

#### Data management

Questionnaires are completed electronically at home using an email link (in accordance with Icelandic data privacy protection for collection and storage), with each participant having codes used for unlocking the questionnaires. These have been divided into separate sessions to minimize the burden on the case participants. The user questionnaires are available in the SmartTrial platform https://www.smart-trial.com/ (research compliant and ethics approved) and are stored at a central database collection center. This procedure has been thoroughly quality-checked by study staff and accepted for privacy and ethics approval by the ethics committee and will secure proper storage of data. Study staff will review the completed surveys within one week of receipt and highlight any missing information. Removing of data will be considered when lacking key data on diet and microbiota or over 50% of data missing. Any issues will be discussed with the principal investigator, the SmartTrial advisory team, and/or the study team. The researchers’ staff will contact the participants no more than three times either via phone, email, or in person at a regular study visit (maximum three times) to remind them to complete questionnaires and acquire answers to missing items.

### Sample collection

All biosamples, except blood, will be collected at home by the participants, with help from their guardians when needed. A biosample kit will be delivered to the participants and collected by research staff to make sure the samples will be in good condition and usable. Participants are asked to collect the biosamples preferably towards the end of the 3-day food registration within the first month into the study and store the biosamples in a specific container in a cool dry place (4–8°C) according to the manufacture’s guidelines. Commercial kits from DNA Genotek´s microbiome stool collection kits are used to collect and optimally stabilize stool samples. Fecal and saliva samples will be collected for microbiome 16s rRNA amplicon sequencing. A buccal swab will be collected for whole-genome genotyping of human DNA. Urine samples will be collected for targeted analysis of food-related peptides and untargeted metabolomics profiling. Blood will be collected either at Landspitali, University Hospital in Reykjavik, or Akureyri Hospital in Akureyri, depending on residence, for analyzing serum zonulin, inflammatory biomarkers, e.g., CRP, interleukins, and nutritional status, i.e., hemoglobin, ferritin, folic acid, Vitamin B_12_, 25-hydroxy-vitamin-D, and fatty acids. The biosamples are preferable to be collected towards the end of the 3-day food registration according to standard procedure as mentioned above. The kit is then collected from both cases and controls by the researchers along with the food diary in Reykjavik, Akureyri, and near surroundings. Participants will be able to deliver the samples to a provided location if they prefer. For other locations in Iceland, the samples will be sent out, including guidelines on how to resend them to the researchers after their collection. The urine samples will be aliquoted into smaller tubes for storing at a laboratory unit at the University Hospital or Akureyri Hospital in a -80°C freezer along with the other biological samples.

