## Introduction

### Mental disorders and intestinal permeability

It has been estimated that up to 20% of children and adolescents worldwide experience mental disorders [1]. Symptoms from the gastrointestinal (GI) tract are common among children with mental disorders [2–4]. Inherent to the rationale of a gastrointestinal role in mental disorders, including imbalanced microbiota, is the idea of intestinal permeability (IP) of the intestinal epithelial barrier. Imbalanced microbiota can result in dysbiosis, which, if left untreated, can affect the intestinal epithelial paracellular pathway [5]. Increased IP allows food-borne chemicals, including toxins, and microbial components, to enter tissues beneath the intestinal lining, which can result in local and systemic inflammation caused by pro-inflammatory cytokines in the intestine as well as outside the intestinal tract [6]. Loss of intestinal barrier function may lead to neuroinflammation and neuroimmune disorders such as autism spectrum disorder (ASD) [1, 4, 7], chronic fatigue syndrome [8], major depressive disorders (MDDs) [9, 10], and schizophrenia [11, 12].

Zonulin, a family of structurally and functionally related proteins, is currently the only known physiologic modulator of intercellular tight junctions and affects mechanisms that regulate the intestinal epithelial paracellular pathway. Zonulin upregulation has been associated with several chronic inflammatory diseases, low-grade inflammation, and autoimmune diseases, including ASD and attention deficit hyperactivity disorder (ADHD), which might have an autoimmune component [1, 13]. There is growing evidence, in genetically susceptible individuals, on changes in the intestinal microbiome composition and function, i.e., intestinal dysbiosis, possibly causing functional changes in intestinal permeability (IP). Functional changes in IP may lead to increased IP, contributing to increased antigen trafficking and break of tolerance, increasing the probability of developing a chronic inflammatory disease [6, 14, 15].

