Intestinal microbiota-derived antigen and endotoxin trafficking from the lumen to the lamina propria has been found to trigger innate-and immunoregulatory responses, which may cause a pro-inflammatory micro milieu. Over time, an adaptive immune response could be mounted, producing pro-inflammatory cytokines, which may cause further opening of the paracellular pathway for the passage of antigens. The specific host genetic background has been found to affect where the inflammatory process will be targeted, i.e., in which organ or tissue [6, 13, 14, 16–18]. Dysbiosis and the presence of inflammation, as well as neuroinflammation, have all been described in mental disorders [13, 19].

The gut-brain axis involves bidirectional communication between the central and the enteric nervous system [20]. Increased IP might affect the enteric nervous system, impacting both mood and behavior [12]. The emerging recognition of the relationship between the gut-brain axis and the neuro-immune system provides a novel approach for potentially better understanding and managing mental disorders. There is an urgent need to investigate these emerging interrelations further.

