Loss of intestinal barrier function may lead to subsequent increased serum levels of microbiota-derived molecules and, in turn, activation of the immune system, which may lead to neuroinflammation. This has been described in several neuroimmune disorders such as ASD [1, 4, 7], chronic fatigue syndrome [8], major depressive disorders (MDDs) [9, 10], and schizophrenia [11, 12].

It is vital to study the intestinal microbiota and IP further regarding diet and mental health [56]. It is important to overcome previous limitations and increase the number of subjects, coordinate strategies, and assess confounding factors, e.g., the severity of the mental disorders and problems from the GI tract, and secure quality collection [94, 122] as well as lifelong medication use. Biosamples will be collected and analyzed with the latest technology factors in addition to the microbiota, that can shed a better light on research questions and potential mechanisms. As data on the gut-brain axis demonstrates association between intestinal microbiota composition and mental disorders such as depression, we will collect fecal samples within this study for microbiome analysis. However, longitudinal studies are lacking, and therefore in this present study, collection of data will be repeated in three years. These are the basis of the current study on Meals, Microbiota and Mental Health in Children and Adolescents, i.e., the MMM study.

Our hypothesis for the current study is the following; There are differences between cases and controls regarding dietary intake, nutritional status and/or the intestinal microbiota and related metabolic factors, in physical symptoms from the digestive tract and in intestinal permeability. In addition, we hypothesize that there are differences in other potentially relevant background factors and therefore comparisons with full siblings will give insight into family variability.

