#### Serum measurements analyses

Concentrations of serum zonulin will be determined by ELISA assays according to the manufacturers’ protocols from Immundiagnostik AG (Bensheim, Germany) but performed at the Mucosal Immunology and Biology Research Center at the Massachusetts General Hospital in Boston. Inflammatory biomarkers will be determined by multiplex immunoassays based on the mesoscale discovery platform (e.g., CRP, interleukins) and nutritional status (hemoglobin, ferritin, folic acid, 25-hydroxy-vitamin-D, ⍵-3 fatty acids) by kits in the Landspitali laboratory in Reykjavik.

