#### Integrative analysis of Meals, Microbiota, and Mental Health data

For each type of omics- and biomarker data (nutrients, microbiota, metabolomics, food-related peptides, inflammatory factors), appropriate preprocessing, and quality control will be coordinated and performed by the researchers. All data will be appropriately normalized and transformed, checked for potential batch effects and outliers removed. The effects of potential confounders such as age, sex, body mass index, ROME IV (for intestinal microbiota), medication, or diet will be investigated. For each datatype cases will be compared to the two control groups, but also associations between the different variables will be looked for separately, as well as in relation to sub-groups, using multivariate models including adjustments for confounder variables. Using analysis of covariance (ANCOVA) the influence of potential confounders such as age, sex, body mass index, ROME IV (for intestinal microbiota), medication and diet will be investigated. Benjamin-Hochberg false discovery rate will be applied, correcting for multiple hypothesis testing.

Integrating different types of high-dimensional omics data is a challenging task, and multiple approaches can be undertaken. A computational framework for such analysis [163] has been suggested based on dimensionality reduction of omics data using co-abundance clustering, followed by cross-omics correlation analysis focused on features that differ between cases and controls. In addition, other types of omics integration approaches will be applied, as recently reviewed [164, 165], such as robust sparse canonical correlation, co-inertia, or Procrustes analysis, to identify shared patterns across omics and dietary data in the context of mental health.

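### Ferritin is treated as a nutritional marker with no inflammatory marker among the named confounders, so lower iron stores in cases may be attenuated or hidden

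*Protocol article*

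**What the plan says.** Two places in the protocol article assign ferritin its role. Sample collection says blood is taken "for analyzing serum zonulin, inflammatory biomarkers, e.g., CRP, interleukins, and nutritional status, i.e., hemoglobin, ferritin, folic acid". Serum measurements analyses repeats the grouping as "nutritional status (hemoglobin, ferritin, folic acid, 25-hydroxy-vitamin-D". Neither qualifies ferritin for inflammation. CRP and interleukins come from the same blood collection but are listed only as inflammatory biomarkers.

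Nutritional status is a compared outcome. The hypothesis, at the end of the section on diet, intestinal microbiota and mental disorders, reads "There are differences between cases and controls regarding dietary intake, nutritional status and/or the intestinal microbiota and related metabolic factors".

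The rationale ties inflammation to case status. Increased permeability "can result in local and systemic inflammation caused by pro-inflammatory cytokines", and "Dysbiosis and the presence of inflammation, as well as neuroinflammation, have all been described in mental disorders".

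On adjustment, the integrative analysis section says that under ANCOVA "the influence of potential confounders such as age, sex, body mass index, ROME IV (for intestinal microbiota), medication and diet will be investigated". It also provides for comparisons "using multivariate models including adjustments for confounder variables". No inflammatory marker is named. Table 1 excludes children with antibiotic use in the previous four weeks but sets no rule on current infection or raised CRP.

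**The concern.** At the same iron stores, an inflamed child shows a higher ferritin than one who is not inflamed. This is general laboratory knowledge and is not stated in the article. Ferritin therefore measures iron stores plus an inflammatory component. The second part cancels between groups only if inflammation is equally common in cases and controls, and the study's rationale points to more of it in cases.

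The two ideas then work against each other in one marker. Less iron in cases would lower their ferritin, and more inflammation would raise it. Age, sex, body mass index, medication and diet do not stand in for current inflammation, so adjusting for them leaves the distortion largely in place. At stake is the reading of one nutritional contrast: a small or null ferritin difference could not be told apart from a real iron deficit offset by inflammation. Ferritin would also carry inflammation, under a nutrition label, into the planned association analyses with the microbiota.

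**Working it through.** **1. The plan's own figure.** The only sample size in the article is 62 per arm for permeability, 30% v 10%, alpha 0.05, power 80%. With pooled variance and a two-sided test:

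n = [1.96·√(2·0.20·0.80) + 0.842·√(0.30·0.70 + 0.10·0.90)]² / 0.20² = (1.109 + 0.461)² / 0.04 ≈ 61.6, so 62.

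This reproduces, but it says nothing about ferritin. The article gives no ferritin SD, no expected difference in iron stores and no prevalence of inflammation, so what follows is illustration.

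**2. Model.** Let R be the true case/control ratio of ferritin at equal inflammation, q the excess share of inflamed cases over controls, and f the factor by which inflammation multiplies ferritin. On the log scale:

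- observed difference d = ln R + q·ln f
- share of the true difference masked = q·ln f / (−ln R)
- power ≈ Φ(|d|/SE − 1.96), with SE = SD·√(2/n)

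**3. Inputs.** n = 100 per group is the article's target minimum. SD = 0.6 on the log scale, R, q and f are all assumed. SE = 0.6·√(2/100) = 0.0849.

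**4. One line in full.** With R = 0.80, f = 1.5 and q = 0.20:

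- Without inflammation, ln 0.80 = −0.2231, and power = Φ(0.2231/0.0849 − 1.96) = 75%.
- With it, the shift is 0.20 × 0.4055 = 0.0811, so d = −0.1421 and the observed ratio is 0.87. Masked share = 0.0811/0.2231 = 36%. Power = Φ(0.1421/0.0849 − 1.96) = 39%.

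**5. Range.**

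| True ratio R | f | q | Observed ratio | Masked | Power, true to observed |
|---|---|---|---|---|---|
| 0.70 | 1.5 | 10% | 0.73 | 11% | 99% to 96% |
| 0.80 | 1.3 | 5% | 0.81 | 6% | 75% to 70% |
| 0.80 | 1.5 | 20% | 0.87 | 36% | 75% to 39% |
| 0.80 | 2.0 | 30% | 0.98 | 93% | 75% to 4% |
| 0.80 | 2.0 | 50% | 1.13 | over 100% | sign reversed |

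Over R = 0.70 to 0.90, f = 1.3 to 2.0 and q = 5% to 50%, the masked share runs from about 4% to beyond 100%.

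**6. A narrower set.** Take q = 20 points, borrowing the 30% v 10% permeability figures purely as a stand-in for inflammation, with f = 1.2 to 1.5 and log SD 0.5 to 0.6. The shift is 0.20·ln f = 0.036 to 0.081, a lift of 4% to 8% in the case geometric mean. Noncentral t power at 100 v 100:

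- true 15% deficit: 48–63% falls to 16–43%, with 22–50% of the log difference masked
- true 20% deficit: 74–88% falls to 38–75%, with 16–36% masked

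The sign does not change anywhere in this set. All power figures are for an unmatched comparison at an unadjusted 0.05; the planned false discovery rate control would lower them further.

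**The case against.** The strongest reply is that the confounder list is given as examples and that adjusted models are provided for, so nothing rules out CRP in a ferritin model. The article may also condense a fuller plan, and covariates for one serum marker are detail that such a plan would hold. This stands as a limit: the article does not exclude the right analysis. It does not remove the point, because the article gives ferritin an unqualified nutritional meaning and does tailor one covariate to one outcome (ROME IV for the microbiota), while the covariate that its own rationale makes most relevant to ferritin is not named.

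A reader might infer more: that lower iron stores in cases will be hidden, or that the contrast will be reversed. The documents support neither. The hypothesis has no direction. The introduction mentions iron and food aversions but predicts no iron deficit in cases. Inflammation is described as possible or as reported, with no prevalence or size. The 30% v 10% concerns permeability, and using it for inflammation is an assumption. Reversal needs much stronger inputs than those in the narrower set.

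Nor does the article say that a null ferritin result would be taken as adequate iron status. Hemoglobin is measured and mineral intake is calculated from the food diary, so ferritin is not the only evidence, although hemoglobin is only a partial second view of iron stores.

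**Conclusion.** The concern holds in a limited form. Adjusted only for the covariates that the article names, the ferritin comparison is open to a bias of known direction: excess inflammation in cases raises their ferritin and may attenuate or hide lower iron stores. The size cannot be derived from the documents. Under assumed inputs it runs from slight (75% to 70% power) to substantial (75% to 39%), and larger only with strong assumptions. The conclusion rests on two conditions that the documents suggest but do not establish: more systemic inflammation in cases, and lower iron stores in cases. If either is absent, no iron deficit in cases is masked. Severity is minor: ferritin is one of many markers, the study is sized on permeability, and the open confounder list leaves room for the correction.

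**What to change.** In the integrative analysis section, state that:

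- ferritin will be analysed on the log scale, with log CRP from the same sample as a covariate in the ferritin model, alongside the covariates already named;
- a sensitivity analysis will be restricted to children whose CRP lies in the normal range, with the limit set before the data are examined;
- the ferritin result will be read together with hemoglobin.

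Keep CRP out of the models for the other hypothesised outcomes. For ferritin as an index of iron stores, inflammation is a measurement disturbance to remove. For permeability, microbiota and related factors it may lie on the pathway under study, and adjusting for it could remove the effect of interest.

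The cost is a few sentences and one covariate in one model, using measurements already planned. The restricted analysis loses the children with raised CRP, and CRP will not capture all inflammation, so some residual bias should be acknowledged.
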